## Abstract

**Background: **More than half of women of reproductive age in India are anemic. Anemia is associated with increased risk of preterm delivery, higher maternal mortality and contributes to fatigue, which affects women’s work productivity. The World Health Organization (WHO) recommends daily oral iron and folic acid (IFA) supplements during pregnancy and weekly supplements for women of reproductive age. Government programs and global donors have distributed and promoted IFA supplements in India for over four decades. However, initial intake and compliance remain inadequate.

**Objectives: **This protocol describes the formative research phase of a larger study, called the Reduction in Anemia through Normative Innovations (RANI) Project, which will test, through a randomized controlled trial, the hypothesis that a social norms-based behavioral intervention in Odisha, India will improve uptake of IFA supplements and reduce anemia among reproductive age women as compared to usual care. The focus of this paper is on the formative research required to develop a sound intervention. We will examine socio-normative barriers to and facilitators of IFA supplement uptake.

**Methods and analysis: **Based on the Theory of Normative Social Behavior, we will adopt a mixed-method, multilevel approach. We will collect data using focus groups, in-depth interviews, observations, Rapid Participatory Ethnographic Evaluation and Research (PEER) techniques, and perceptual mapping methods. Our sample includes reproductive age women (pregnant and not pregnant), their husbands, their mothers/in law and key stakeholders. Before collecting the data, and after analyzing the results, we will hold convenings in India to engage key stakeholders in collaborative design. Following the intervention design, we will test components of the intervention, gather user feedback and fine-tune as necessary.

**Impact: **This study will contribute to the social norms and behavioral intervention research and inform policymakers about the value of adopting a socio-normative approach.

## Introduction

Anemia is a condition where the number of red blood cells and their oxygen carrying capacity is insufficient to meet the body’s physiological needs
^1^. Iron deficiency is the most significant contributor to the onset of anemia
^2^. Globally, anemia affects 1.62 billion people, which corresponds to almost 25% of the population. While young children and pregnant women have the highest rates of anemia, non-pregnant women make up the greatest number of individuals with anemia
^3^.

Anemia can lead to poor physical capacity and performance, influencing work productivity as well as increasing risk of preterm delivery and higher maternal mortality
^2,
4^. Maternal anemia could also lead to infantile iron deficiency, negatively affecting children’s physical and cognitive development
^5,
6^. Iron-deficiency anemia among women of reproductive age (WRA) leads to a substantial double burden on the potential economic development and well-being of the population. Near-term consequences of anemia among WRA include reduced labor productivity and non-workplace activity (e.g. child care, household maintenance, leisure-time physical activities) due to fatigue
^7^. In the longer term, iron deficiency during pregnancy and early childhood causes permanent reductions in children’s cognitive capacity and socio-emotional functioning that will impact their productive capacity across the life course
^8,
9^.

Anemia is a significant public health problem in India
^10^, with more than half of its women between 15 and 49 years diagnosed with the condition
^11^. Reasons for these are multifactorial and include consumption of a predominantly plant based diet
^12^; micronutrient deficiencies, such as vitamin B12
^13,
14^; and hookworm and malarial infections
^15,
16^. Physical and cognitive productivity losses associated with anemia in India are estimated to be 6% of Gross Domestic Product (GDP )
^17^. 

In 2012, the World Health Assembly Resolution 65.6 endorsed a Comprehensive Implementation Plan on Maternal, Infant and Young Child Nutrition (CIP), with six Global Nutrition Targets for 2025, with its second target aiming for a 50% reduction of anemia in WRA (15–49 years)
^18^. Taking iron supplements prevents anemia, and in low-income, predominantly vegetarian countries where anemia rates can be severe, it is more efficacious than increasing consumption of iron rich foods
^19^. The WHO recommends daily oral iron and folic acid (IFA) supplements during pregnancy and weekly supplements for women of reproductive age
^20^.

### Current government led programs to reduce anemia in India

India has implemented several programs to tackle anemia, the first of which is the National Nutritional Anemia Control Program, implemented in 1970, to promote regular consumption of iron rich foods and to provide iron and folic acid (IFA) supplements to pregnant and breastfeeding women
^21^. Since that time, although many nutritional programs exist in India, only few focus on anemia control.

The emergence of two programs followed in 2000, one is the Weekly Iron and Folic Acid Supplementation (WIFS) program, which provides weekly IFA supplements to adolescents through The Adolescent Girls Anemia Control Program
^22,
23^. Following this, the 12 by 12 initiative was launched in 2007 with the goal of making sure every child in India achieves a healthy hemoglobin level within 12 years
^23^. 

The Ministry of Health and Family Welfare also developed the National Iron+ Initiative Program (NIPI) to address supplementation interventions for pregnant and lactating women and supplementary nutrition for pregnant, lactating women and adolescent girls to increase protein intake
^24^. In addition to the existing programs, several researchers have designed and conducted randomized controlled trials in India to reduce anemia in WRA
^25–
28^.

Despite universal distribution and receipt, the intake of the IFA supplement remains low. Data from the 2015–2016 cycle of the India Demographic Health Data show that 91 percent of pregnant mothers reported that they received IFA supplements during their last pregnancy but only 37 percent consumed them for more than 100 days during pregnancy. Clearly, there are significant demand side barriers that contribute to low uptake and compliance.

### Barriers and facilitators to IFA uptake and compliance

Several studies, including recent investigations in Kenya and Nepal have indicated that
*knowledge barriers* exist, with women reporting that they did not receive adequate information from their providers when they distributed their IFA tablets
^29,
30^. A summary of four qualitative studies in India showed that in each study, many women did not know the importance of consuming iron supplements or the link between anemia and iron supplements
^31^. Another recent study in India, reported that pregnant women were unaware of the association between anemia and maternal outcomes
^32^.

Perceived and real
*side effects* have also been implicated by numerous studies as being critical barriers. Specifically, adolescents and WRA reported that side effects include gastric problems, stomach pain, weight gain and nausea
^33,
34^. Additionally, pregnant women in India report beliefs that taking too much iron may cause too much blood or a large baby, making labor more challenging
^32,
35^.

The WHO has expressed concern that the current
*dose of 100mg IFA supplement* for women in India is higher than their recommendations and may therefore itself be a barrier to use
^10^. And despite the demonstrated acceptability of weekly or twice weekly supplementation in smaller trials and state-level pilot programs in India, the 2012 national scale-up of weekly IFA supplementation with 100mg iron targeting school-age youth has met resistance due to concerns regarding the gastrointestinal side effects
^36^.

Additional barriers in reducing anemia include food insecurity, which may result in a
*poor-quality diet*. A 2002 qualitative study conducted in developing countries reported that dietary restrictions could vary across gender as a woman reported, “eating last” or eating “whatever is leftover” as reasons for inadequate diet
^37^.

WRA do not make decisions about their health in isolation;
*social networks* can influence behaviors and family members play a crucial role in supporting the use of IFA tablets in women
^38^. Pregnant women whose spouses actively participated in antenatal visits were more likely to demonstrate a significantly higher adherence to IFA supplements than women whose husbands were not active throughout antenatal visits
^39^. Mothers and mothers-in-law can also influence the intake and adherence of IFA in pregnant women, even more than their partners as demonstrated by a formative research study among pregnant women in Bangladesh. However, when it came to money matters, husbands were involved and considered the most important decision-makers
^40^. Financial decision-making and control within a family may also have implications on a woman’s ability to obtain IFA tablets.

A growing body of literature points to social norms as a critical barrier to IFA uptake
^41,
42^. Social norms are mores or rules of behavior that are considered acceptable in a group or society
^43^. Evidence from a meta-synthesis of qualitative research on the social determinants of iron supplementation among WRA conducted in 17 countries identified social norms as one of the primary factors limiting uptake of iron supplements, particularly during pregnancy
^10^. However, to our knowledge, no studies have used a social norms approach to reduce anemia
^36^.

Social norms are different from laws in that they are negotiated through social interactions, whereas laws are codified. Traditions, like social norms are also socially negotiated, but they are more stable. The primary difference is that norms are more dynamic, and shaped and understood through communication processes
^44^ and can thereby be shaped to promote positive healthy behaviors
^45^.

Lastly, the policy context can also act as an enabler or as an obstacle for the spread of evidence-informed IFA policy innovations. The adoption of new evidence and its consideration by domestic policy actors and stakeholders remains a complex challenge for the translation of empirical evidence into policy implementation. The evidence-to-action gap is “stickier” in cases of multi- and trans-disciplinary research programs and in research programs, such as this, that deal with complex, inter-sectorial issues
^46,
47^. These challenges have been studied from various disciplinary perspectives including diffusion of innovation theory
^48,
49^ comparative policy and political science studies
^50,
51^, knowledge utilization theory and evaluation influence studies
^52–
54^, and the science of team science
^52^, among others. What has received less attention, and what comprises a significant focus of this project, are the socio-normative factors that guide policymaking. Two major knowledge gaps are of particular relevance to this study. The first is the need to better characterize the channels and mechanisms through which potential changes in population-level social norms around anemia and IFA use percolate upwards to redesign existing national and state-level policies. The second is the challenge of facilitating the adoption and utilization of the research evidence by policy actors and stakeholders in Odisha leading to system learning and improved performance in IFA policy implementation.

## Conceptual framework

Given the presence of multilevel demand side barriers to IFA use, including social norms themselves, the Theory of Normative Social Behavior (TNSB)
^55^ will underpin the formative research and subsequent intervention. The TNSB can help elucidate
*when*,
*how and which* norms affect health behaviors
^46^. Two key features of TNSB are particularly important. One is the distinction
*between descriptive norms* and
*injunctive norms*. Descriptive norms refer to individuals’ beliefs about what other people do and how often they do them. Injunctive norms are what individuals believe that others expect them to do. Descriptive norms are thought to influence behavior because of people’s desire to do the right thing or the thing that they believe most people are doing
^56^. Injunctive norms are thought to influence behavior because of individual’s motivations for connection with others
^57^. A second key feature of the TNSB is the distinction between
*collective norms* (defined as a property, characteristic or behavior within a group of people) and
*perceived norms* (defined as individual beliefs about other people’s actions and expectations). A key difference between the two is that collective norms operate at the societal or social network level whereas perceived norms operate at the individual level. While collective norms, which can be thought of as aggregated individual behaviors in a group, may influence perceived norms, there may be a discrepancy between what people in the group actually do and what an individual perceives that they do. For example, women of reproductive age in Odisha may believe that most women do not take IFA tablets when, in practice, many women do. Changing perceived norms around women taking IFA tablets to align with collective norms is one potential approach.

According to the TNSB, it is important to assess the source of normative influence, whether it is one’s peers, family members, or other influential people, because the closer the social distance between oneself and the referent others, the stronger the influence
^46^. This study points to the influence that mothers/mothers-in-law and husbands have on women’s likelihood to take IFA supplements. Finally, the TNSB states that the impact of norms has to be evaluated in the context of people’s aspirations to emulate others around them, the level of similarity they feel with them, the extent to which they believe they will receive benefits by engaging in the behavior, and whether they believe social sanctions will be imposed if they fail to comply. This has important implications for our formative assessment, as it points to the importance of understanding how WRA and their social network members think about IFA in terms of the costs and benefits, pressures to conform, and possible linkages between IFA or anemia and their future aspirations.

The overall effort is named the RANI Project, which stands for Reduction in Anemia through Normative Innovations.

### Research methods and analysis

***Aims and objectives***. By the end of the formative assessment period, we will have designed, adaptively tested, and refined an intervention that can be feasibly and effectively implemented to reduce iron-deficiency anemia among women of reproductive age and pregnant women in Odisha, India. To achieve this goal, the formative assessment has the following aims:

1. At the community level, to identify key contextual, administrative, policy, and service environments that either facilitate or hinder access to and use of IFA supplements among women of reproductive age and pregnant women2. At the interpersonal and individual levels, to identify norms, referent groups, and the extent to which they act as barriers or facilitators to IFA use and compliance among reproductive age women and pregnant women3. To design, pilot test, and subsequently modify and finalize an intervention to increase IFA use and compliance and to reduce anemia among reproductive age women (with a focus on transforming harmful norms and promoting beneficial norms)

The formative assessment will be conducted from March to December, 2018. After analyzing results, we will hold a convening workshop in July, where we will formulate a first draft of the intervention plan. We will pilot test the various components of the intervention to determine its feasibility and effectiveness. Findings from these pilot evaluations will inform and refine the intervention, which we will finalize by December, 2018.

Figure 1 depicts the formative research workflow.

**Figure 1. f1:**
[figure not shown]
Formative Research Workflow.

## Research setting

### Odisha, India

Odisha is an eastern Indian state on the Bay of Bengal (
Figure 2). According to the 2015–2016 India Demographic Health Survey, 83% of households in Odisha reside in rural areas and 67% of women and 84% of men are literate. The vast majority of household heads are Hindu (95%) and 23% of households belong to a specific tribal culture. The total fertility rate (TFR) in Odisha is 2.1 children per woman. In the last five years, 60% of pregnant women had four or more antenatal care visits and 82% of women delivered in a health facility. About half (51%) of women in Odisha have anemia with a higher rate for women from a tribal culture, those following the Christian faith, and those with no schooling
^58^.

**Figure 2. f2:**
[figure not shown]
Geographic Location of Study.

### Research team

We will conduct the research as a close partnership between the George Washington University (GW), IPE Global, our implementing partners based in Delhi and DCOR Consulting, a research firm based in Odisha, India. The research team consists of university-based researchers with expertise in qualitative research, social norms and global behavior change interventions. IPE Global and DCOR Consulting also has expertise in nutrition and SHG focused interventions in Odisha. These partnerships will be instrumental to gain access to the community and to understand the local context.

## Research design

Qualitative inquiry can improve the description and explanation of complex, real-world phenomena related to attitude and behavior change. Quantitative research alone is often insufficient to understand these complicated processes
^59,
60^. Our research team proposes to examine
*why* IFA supplement use is low despite recommendations from the government and existing programs promoting its uptake and
*which* existing social norms promote or hamper uptake. Additionally, surveys and quantitative methods have been the primary tool to test theories on social norms and to understand the prevalence of existing norms in communities
^61,
62^. Some theorists have suggested that more qualitative research would be useful in illuminating the process of social norm change in different situations
^63^. We respond to that call.

### Data collection modalities

We will collect qualitative data via in-depth interviews, focus groups, Participatory Ethnographic Evaluation and Research (PEER) interviews, and structured observations.

***In-depth interviews and focus groups.*** We will conduct in-depth interviews with key informants including Self-help group (SHG) leaders, health providers, teachers and health officials. We will conduct focus groups with women of reproductive age (including pregnant women), spouses, mothers, and mothers-in-law. Prior to focus group interviews participants will complete a demographic questionnaire including questions about caste. We plan to conduct approximately sixteen focus groups and twenty-four key informant interviews but the final sample size will be determined based on theoretical saturation
^64^.
Table 1 shows the expected number of interviews and focus groups.

**Table 1. T1:** Expected Number of interviews and focus groups. Preliminary Schedule of Focus Group Discussions (FGDs) and In-depth Interviews (IDIs).

Participants	Session type	# Sessions	# Participants
Self-help group leaders	IDI	4	1
Government/ministry representatives	IDI	4	1
Antenatal service providers	IDI	4	1
Secondary school teachers	IDI	4	1
Traditional Healers	IDI	4	1
Anganwadi/ASHA workers	IDI	4	1
Adolescents of reproductive age (15 – 19) years old	FGD	4	6–10
Women of reproductive age (20 – 35) years old	FGD	4	6–10
Married men (18 – 42) years old	FGD	4	6–10
Mothers-in-law	FGD	4	6–10

***Observational Data.*** Observation can allow the researcher to draw inferences about a phenomenon that they cannot obtain from direct conversation via interviews or focus groups. We will collect observational data from four venues: antenatal care (ANC) clinics, medicine stores/pharmacies, self-help groups, and outdoor food markets. Data collectors will take notes on a standard observation form (See
Supplementary File 3) at one of each of the following four venues in each of the four villages (16 observations total):

Medicine store/pharmacy observations will note how well IFA tablets are stocked, where they are stocked within the store, the extent to which they are purchased, their price, and their packaging.

ANC clinic observations will note whether there are existing communications (e.g. health education posters) about anemia and/or IFA supplementation. They will also record notes on the environment including (cleanliness, crowding, wait-time, etc.). Additionally, they will observe the pharmacy within the ANC clinic and note how many IFA tablets are available, cost, packaging and stocking/stock outs. We will not inform clinic staff about the observation prior to arrival to ensure that we observe the facility in its authentic state.

Data collectors will observe SHGs and take notes about the nature of their interactions with women in the community. They will take note of how well they function, what they discuss; the kind of activities that they undertake and any challenges that they face.

Data collectors will observe outdoor food markets, as diet is an important factor to consider while studying iron-deficiency anemia. We will take photos of all food items in the market; list them out and inquire about the cost of each item.

***Perceptual Mapping.*** We will conduct perceptual mapping exercises to obtain a visual model that depicts how women and their influencers (their spouses/partners, their mothers-in-law, and others in their social network) think about IFA supplements, anemia, and other related factors, including physical and mental fatigue, and diet (see
Supplementary File 4). Perceptual mapping is a technique used to elicit a mental picture held in common by members of a group. Perceptual mapping helps us understand how people construe various objects, both in terms of what meaning they give to them and how they construe the objects in relation to one another
^65,
66^. Perceptual mapping is done in three steps – attribute elicitation, scoring, and mapping.

*Step 1: Attribute Elicitation.* The purpose of this step is to extract the meaningful attributes with which people construe specific objects. For example, if people are asked to list a significant attribute pertaining to “IFA tablets,” some may point to “awful taste” as the primary attribute. For others, IFA tables may represent the idea of “medication for a better tomorrow” or “healthy” as the primary attribute. Knowing these key attributes will help us craft meaningful messages during the intervention phase. For example, we may be tempted to develop messages about IFA uptake on the assumption that it represents “no anemia” in the minds of participants. It may well be, however, that the primary attribute pertaining to taking IFA supplements for certain women may center around issues of forgetfulness or something whose impact is not easily visible. If this is the case, then our messages about IFA supplementation would be far less effective than those that tackle the issue from the perspective of linking it with more immediate positive outcomes.

For attribute elicitation, we will provide two images (on two cards), one being a reference object, of particular objects and ask people to tell us how similar or different the two are from each other (on any dimension that the participant uses). Subsequently, the reference object will be kept the same, but another second object will be shown and the same comparison will be solicited. This process will be done for all permutations of all object pairs. We anticipate having 12 objects, for a total of 55 comparisons. The objects we have currently include: IFA pill; clinic; medicine store/pharmacy; SHG; traditional healer; physicians; fatigue; prenatal care; green vegetables; meat; money; and nausea/diarrhea.

*Step 2: Scoring.* A handful of attributes are thus identified for each primary behavior of interest. Respondents are then asked to rate the importance of each attribute for each behavior or object.

*Step 3: Mapping.* Step 2 results in a
*p* (number of attributes) x
*q* (number of behaviors or objects) matrix that is then used to model the relative distances between behaviors or objects on a
*p*-dimensional plane, thus showing the relative distances among behaviors or objects. Two behaviors or objects close to each other on a particular attribute signify their conceptual proximity. This mapping provides an understanding about how the primary behaviors or objects of interest are understood by the audience; it also specifies the relative distances among objects.

Three perceptual mapping exercises will be conducted: one among women of reproductive age (including pregnant women), one among men (who constitute the support group for the women), and one among mothers/mothers-in-law and sisters or sisters-in-law. Approximately 30 individuals per group will participate in the mapping exercise, for a total of 90 individuals.

***Rapid PEER.*** We will also conduct Rapid Participatory Ethnographic Evaluation and Research interviews (Rapid PEER), which will enable us to gain local insights into the beliefs and behaviors of beneficiaries, in the full context of their lived experience. This unique ‘insider perspective’ will ensure intervention is truly designed with the user in mind. We will train ‘ordinary’ members of the target group, in this case pregnant women and women of reproductive age, their spouses, and their mothers/mothers-in-law, after which they will serve as Peer Interviewers
^67,
68^.

To execute the Rapid PEER, we will train Peer Interviewers to carry out in-depth conversational interviews designed to obtain targeted information from others in their own social group. We will decide on five key questions that form the structure of the conversational interview process. The Peer Interviewers themselves will suggest how to form the questions from formal Odia language into a more conversational format. Non-literate Peer Interviewers will draw pictures to represent each of the five questions. We will ask the same questions at each site to at least two interviewees from the PEER interviewers social group. The informal wording and pictures to remember and ask the question may vary to suit the preference of the Peer Interviewers.

Data collection will be carried out over a one-day period, wherein the PEER interviewers will hold conversations with two same-sex friends who fit the inclusion criteria (pregnant women, women in the reproductive age group, their spouses or mothers/mothers-in-law, all living in the community, 15 years of age or older who speak Odia). Within 24 hours, researchers will debrief the PEER interviewers to obtain detailed in-depth information from each PEER interviewer on what they discussed during the interview. During the debriefing process, the research team will probe PEER interviewers for broader contextual information regarding the responses during the interview. A final workshop with PEER interviewers will explore their experiences of assisting with the formative research.

The Rapid PEER process will take 4 days at each site (two villages total):

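### Perceptual-mapping distances are built from importance ratings, which do not record whether or in which direction an attribute describes an object, so opposites can be mapped as close

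*Protocol article*

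**What the plan says.** The protocol article describes perceptual mapping in three steps under Data collection modalities. Its declared purpose is to learn what meaning people attach to objects and how they see the objects in relation to one another.

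- **Step 1 (attribute elicitation).** Interviewers show pairs of objects and "ask people to tell us how similar or different the two are from each other". The answers are used to extract attributes. The examples given are that "some may point to “awful taste” as the primary attribute", while for others "IFA tables may represent the idea of “medication for a better tomorrow” or “healthy” as the primary attribute".
- **Step 2 (scoring).** "Respondents are then asked to rate the importance of each attribute for each behavior or object". The article gives no response scale, anchors or direction.
- **Step 3 (mapping).** Step 2 yields an attributes-by-objects "matrix that is then used to model the relative distances between behaviors or objects on a" plane with one dimension per attribute, "thus showing the relative distances among behaviors or objects". The reading rule follows: "Two behaviors or objects close to each other on a particular attribute signify their conceptual proximity".

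The Analysis section adds that the mapping data will be analysed by multidimensional scaling, that the resulting dimensions will be compared with the qualitative themes, and that the team will then settle on a dimension judged valid and useful for the intervention. The mapping exercise is referred to Supplementary File 4, which is not available here.

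**The concern.** The exercise sets out to measure meaning, but the score as worded measures salience. These come apart when an attribute matters for two objects for opposite reasons. Taste could be rated very important for the IFA pill because it is disliked, and for meat because it is enjoyed. The object list makes such pairs realistic: the IFA pill, green vegetables and meat stand beside fatigue and nausea/diarrhea, and an attribute about health could plausibly be rated important for all five. A low score is also ambiguous, since it may mean that the attribute does not apply or that it applies but does not matter.

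The importance matrix is the only stated input to the distances, so nothing else in Step 3 would restore the missing direction. What is at stake is the interpretation of the three maps. Closeness would be read as shared meaning when it may reflect only shared salience, and the dimension chosen for its usefulness to the intervention would come from that configuration.

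**Working it through.** The plan states no figure to reproduce. The check sets the three steps side by side and then uses assumed ratings to see when the problem arises and when it does not.

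**1. Aim, measurement and reading.** The aim is how objects are construed. The measurement is importance of attribute for object. The reading is that closeness equals conceptual proximity. The reading follows from the measurement only if importance rises and falls with how well the attribute describes the object. The article does not state or secure that link.

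**2. A two-sided attribute (assumed scales).** Let an object's true position be x, from −2 (bad pole) to +2 (good pole), and let undirected importance on a 1-to-5 scale be 1 + 2|x|.
- Objects at x = +2 and x = −2 have importance 1 + 2·2 = 5 and 1 + 2·2 = 5, so the distance is |5 − 5| = 0.
- On a directed rating the distance is |2 − (−2)| = 4, the whole range.

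**3. Two single-pole attributes (assumed 1-to-5 scale).** Take *awful taste* and *healthy*, with two opposite objects.
- If respondents treat importance as association, the ratings are (5, 1) and (1, 5). The distance is √[(5 − 1)² + (1 − 5)²] = √32 = 5.66, and the opposites are kept apart.
- If they treat importance as salience, so that *healthy* is very important for an object because the object is the reverse of healthy, both can be rated (5, 5). The distance is then 0.

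Single-pole labels therefore help, but only if respondents answer a question somewhat different from the one written.

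**4. Effect on a whole map (simulation on assumed ratings).** The inputs were 12 objects (the article's anticipated number) and 5 or 8 attributes (assumed; the article says only that there will be a handful). True positions were drawn with equal probability from the integers −2 to +2. Each undirected attribute was replaced by 2|x| − 2, which keeps the same range. Euclidean distances (assumed; the article names no metric) were computed between all pairs of objects. The table gives the mean Spearman correlation between true and mapped distances over 1,000 runs.

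| Attributes | Number undirected | Mean rank correlation |
|---|---|---|
| 5 | 0 | 1.00 |
| 5 | 1 | 0.76 |
| 5 | 2 | 0.55 |
| 5 | 4 | 0.17 |
| 5 | 5 | 0.01 |
| 8 | 0 | 1.00 |
| 8 | 2 | 0.70 |
| 8 | 4 | 0.43 |
| 8 | 6 | 0.20 |
| 8 | 8 | −0.01 |

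The result runs from no loss to a map that carries no information on the true distances. The deciding quantity is the share of attributes rated without direction, and the document does not give it. With few attributes, even one undirected attribute has a visible effect.

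**The case against.** The strongest reply is that the harm is conditional. The article's own example attributes are single-pole, so the direction sits in the label, and a respondent who rates *awful taste* high for the pill and low for meat already separates them. That stands: it is the 5.66 case above. It does not dispose of the point. Step 1 lets participants compare objects on any dimension they choose, and no rule makes the resulting attributes single-pole. The prompt as written also does not ask for association.

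Second, the instrument is not visible. Supplementary File 4 may already word the item as description, and the Instrument development section says all instruments will be tested and revised in the pilot. This also stands. The fault may lie only in the article's sentence, and the absence of direction in the instrument itself cannot be confirmed.

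Third, a reader might infer that the intervention messages will be built on false proximities. The documents do not support that. The article ties messages to the elicited attributes: "Knowing these key attributes will help us craft meaningful messages during the intervention phase". The map dimensions are compared with qualitative themes before one is chosen, findings are triangulated and taken back to participants and stakeholders, and the intervention components are pilot tested. What remains is narrower. The comparison with themes concerns dimensions, so it may catch some errors, but it does not directly test the object-to-object distances.

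Fourth, a reader might regard Step 1's similarity judgements as a neglected direct input for multidimensional scaling. Their stated purpose is to elicit attributes through open comparison. Turning them into numeric dissimilarities would be a different design, and leaving them out of the distances is not an error.

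**Conclusion.** The point holds in conditional form. Read as written, Step 2 collects salience, Step 3 builds distances from that alone, and the article interprets closeness as shared meaning. Objects construed in opposite ways can therefore be mapped as close on any attribute that is two-sided, or that matters because the object is its opposite.

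It does not follow that such objects will be mapped as close, or that all three maps and all 90 participants are affected. The size is unknown and may be nil. The contrast of 0 with 4 and the simulated correlations rest on assumed scales, an assumed number of attributes and an assumed form of undirected answering. They show the possible range and are not an estimate for this study.

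The consequence is modest, because the component is formative and triangulated and bears on no trial endpoint. It is still worth correcting, because the correction is cheap and brings the measurement into line with the stated aim.

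**What to change.** Before the pilot:

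1. Change the Step 2 prompt to ask how well each attribute describes each object. Use single-pole attribute labels, or a signed scale with fixed anchors where an attribute has two poles.
2. Build the Step 3 map from those descriptive ratings.
3. If importance is wanted, ask it separately, once per attribute, and use it as a weight.
4. If Supplementary File 4 already asks for description, leave the instrument alone and correct the article's Step 2 sentence.

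The cost is a reworded prompt and response card, plus at most one optional importance item per attribute. The respondents and the number of attribute-by-object ratings stay the same, and the planned pilot revision of instruments already gives the occasion. Recording the Step 1 similarity answers on a short numeric scale is an optional extra and is not needed to resolve this point. It would add one recorded number for each pair judged.
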